## 4. Conclusions

This paper provides a roadmap for using historical controls and setting up multi-center, multi-national pragmatic trials in real-life settings for diseases such as TB that take a long time to treat and follow up, and for which research resources are rather scarce. We believe that the results from the RIAlta study will inform future, larger trials and thus contribute to the generalization of the use of optimized doses of rifampicin in the real-world setting.

## 5. Trial Status

The trial is registered with the EudraCT number 2020-003146-36 and the NCT04768231. Site initiation visits and the recruitment of the first participants are expected to start in the last quarter of 2022 or first quarter of 2023. 

## Figures and Tables

**Figure 1 pharmaceutics-15-00009-f001:**
[figure not shown]
Study flow diagram.

**Table 1 pharmaceutics-15-00009-t001:** Comparison of recent phase 2 trials using high-dose rifampicin for tuberculosis.

Study	Trial ID	Design	Population	Key Exclusion Criteria	Arms	Max. Rifampicin (mg/kg/day)	Follow-Up (Weeks)
Ruslami 2013	NCT01158755	Phase 2b, open label, randomized	≥15 years old with clinically suspected TB meningitis	Body weight < 30 kg, liver disease	2	13	26
HR1	NCT01392911	Phase 2a, open label, sequential allocation	18–65 years old with confirmed pulmonary DS-TB	High alcohol consumption, diabetes	7	50	2
RIFATOX	ISRCTN55670677	Phase 2b, open label, randomized	18–65 years old with confirmed pulmonary DS-TB	High alcohol consumption, diabetes, HIV	3	20	16
HIGH RIF-2	NCT00760149	Phase 2b, double blind, randomized	18–65 years old with confirmed pulmonary DS-TB	Body weight < 50 kg, clinical hepatitis/cholestasis	3	20	12
MAMS-TB	NCT01785186	Phase 2b,c, open-label, randomized	≥18 years old with confirmed pulmonary DS-TB	High alcohol consumption, HIV infection with <200 CD4	5	35	48
HIRIF	NCT01408914	Phase 2b, double blind, randomized	18–60 years old with confirmed pulmonary DS-TB	Body weight < 30 kg, viral hepatitis	2	20	26
RifT	ISRCTN42218549	Phase 2, open label, randomized	≥18 years old with clinically suspected TB meningitis	Cirrhosis or clinical jaundice	3	35	24
RIFAVIRENZ	NCT01986543	Phase 2, open label, randomized	≥15 years old with confirmed pulmonary DS-TB	AIDS-defining infection, pharmacological immunosuppression	2	20	28
RIAlta	NCT04768231	phase 2b,c, open label, historical controls	≥60 or ≥18 years old (with HIV, HBV, HCV, DM), pulmonary and extrapulmonary TB	Decompensated chronic liver disease, oral anticoagulation	1	35	72

**Table 2 pharmaceutics-15-00009-t002:** Analysis populations and endpoints.

Assessment	Primary Safety	Efficacy
1. Per protocol population	Includes participants who completed assigned follow-up AND were at least 80% adherent to study treatment.	Includes those participants who complete assigned follow-up AND were at least 80% adherent to study treatment.
2. Intention to treat population	Includes all the participants that received at least one dose of anti-TB drugs.	Includes all the participants enrolled in the study.
3. Modified intention to treat population	Includes a subset of intention-to-treat population with exclusion of some subjects in a justified way (subjects having non-tuberculous mycobacteria, early withdrawal of consent, etc.).	Includes subset of intention-to-treat population with exclusion of some subjects in a justified way (participants having non-tuberculous mycobacteria, early withdrawal of consent, etc.).
4. Microbiological intention to treat population	Includes all the participants that received at least one dose of anti-TB drugs AND have culture confirmation of DS-TB.	Includes all the participants enrolled in the study AND have culture confirmation of DS-TB.
5. Microbiological per-protocol population	Includes those participants who complete assigned follow-up AND were at least 80% adherent to study treatment AND have culture confirmation of DS-TB.	Includes those participants who complete assigned follow-up AND were at least 80% adherent to study treatment AND have culture confirmation of DS-TB.

**Table 3 pharmaceutics-15-00009-t003:** Weight-band dosing of rifampicin.

High Dose Rifampicin (35 mg/kg)	Weight-Band Dosing					
	35–40 kg	41–50 kg	51–60 kg	61–70 kg	71–80 kg	≥80 kg
**Rifampicin tablets** (300 mg)	900 mg 3 tablets	900 mg 3 tablets	1500 mg 5 tablets	1500 mg 5 tablets	1800 mg 6 tablets	2400 mg 8 tablets
**Rifampicin tablets** (150 mg)	-	150 mg 1 tablet	-	150 mg 1 tablet	150 mg 1 tablet	-
**Fixed dose combination** (*150 mg rifampicin, 75 mg isoniazid, 400 mg pyrazinamide, and 275 mg ethambutol*)	450 mg 3 tablets	450 mg 3 tablets	450 mg 3 tablets	600 mg 4 tablets	750 mg 5 tablets	750 mg 5 tablets
**Total rifampicin dose**	1350 mg	1500 mg	1950 mg	2250 mg	2700 mg	3150 mg

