### 2.5. Recruitment

Participants will be prospectively included and compared with historical controls from the same sites. Participants meeting all the inclusion and not any of the exclusion criteria will be offered to start on the HR^35^ZE arm. After 8 weeks, participants will be managed according to the national TB guidelines.

The selected retrospective participants will provide a comparison for the primary safety outcome, and to the secondary efficacy outcome of culture conversion at 8 weeks using MGIT media. 

We adhered to all Pockock’s principles for historical controls except for the use of information from participants that were previously randomized in clinical trials [23]. To avoid the selection bias that may arise because of this limitation, we aim to include all adult patients fulfilling the inclusion criteria treated with HR^10^ZE in the participating sites between January 2017 and December 2019 (to avoid the influence of the 2020–2021 SARS-CoV-2 pandemic in TB diagnoses and follow-up). Thus, the records of all patients from that period with pulmonary and extrapulmonary rifampicin susceptible tuberculosis will be reviewed. We will capture the severe or grade 3 adverse events and week 8 microbiological status from those who are ≥60 years, or ≥18 years and have a diagnosis of diabetes, malnutrition, HIV, HBV or HCV coinfection, other stable chronic liver diseases, or TB meningitis, and have no pharmacological immunosuppression. We intend to control the retrospective cohort to match the prospective one for age, sex, cavitation in lung TB, and severity in TB meningitis. In case not enough matched controls are not found, we will extend the search with patients until the calculated sample size in the control arm is achieved. The historical cohort will include participants from only Spain, Portugal, and Paraguay and not likely from the Netherlands, as optimized doses of rifampicin have been used in both Dutch sites for more than a decade in the same participant subgroups as included in our study.

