### 2.8. Assessment of Study Outcomes, Analysis Groups, and Duration of Follow-Up

The primary safety hypothesis is that the incidence of adverse events in the high dose rifampicin (35 mg/kg) supplemented with isoniazid, pyrazinamide, and ethambutol [HR^35^ZE] during the first 8 weeks of treatment will not exceed that of controls on a standard HRZE regimen (rifampicin 10 mg/kg) [HR^10^ZE]. The HR^35^ZE regimen will be considered unsafe if in a non-inferiority analysis, the upper limit of the 95% confidence interval of the difference of proportions in grade ≥ 3 AE (according to CTCAE scale version 5) between the experimental and the historical control arm exceeds 8%. The most common adverse events related to therapy with higher rifampicin doses were vomiting, headache, hyperuricemia, pain in the extremities, and pruritus. No significant differences according to rifampicin dose (from 10 to 35 mg/kg) were found in a recent systematic review and in a retrospective study collecting the real-life experience from a Dutch center [24,25].

To assess the AE and ensure a homogeneous evaluation of their grade, severity, expectedness, and treatment relatedness, we will administer a standardized training for the investigators from all different sites. In addition, both for the prospective and the retrospective cohorts, grade 3 or higher adverse events and SAE will be reviewed by the trial’s Steering Committee for relatedness classification. When no consensus is reached, the Data and Safety Monitoring Board formed by experts independent from the trial will make the final decision.

Tolerability will be measured as any adverse event (grade 1 to 4), treatment dropout rate, and any dose reduction. For efficacy outcome, the hypothesis is that in DS-TB participants (pulmonary disease), the proportion of participants experiencing successful treatment outcomes (culture and smear negative) at the end of the intensive phase of treatment on HR^35^ZE will be non-inferior to that of controls on HR^10^ZE. The HR^35^ZE regimen will be considered ineffective if the lower limit of the 95% CI of the proportion of participants with a negative sputum culture (sputum sterilization), or unable to produce sputum if they have a previous negative culture at week 8, is more than 10% lower than that of historical controls treated with HR^10^ZE. Other exploratory outcomes will be reported descriptively. 

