### 2.9. Sample Size Assumptions and Justification

For the sample size calculation, a non-inferiority design is assumed and the upper limit of the 95% confidence interval (CI) of the difference of proportions in grade 3 or higher adverse events at 8 percentage points has been set. We assume that 5% of patients will not be assessable. Alpha risk is set in 0.1 and power in 0.8. Based on the previous literature and our previous experience, expected standard treatment grade ≥ 3 AE are 5–10% (mean 8%) among experimental arms and standard treatment arms. Considering this, the number of participants per arm has been calculated to be 134 participants. Because of the limited recruitment capacity for this trial, we could not target specific numbers of participants for each sub-group of risk factors. 

Based on a feasibility survey performed at the planning stage, the target enrollment rates per country were: Paraguay 6.25 participants per month; Spain, Portugal, and the Netherlands 1.6 participants per month.

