### 2.10. Main Outcomes Analysis

The primary safety outcome will be analyzed as the proportion of participants in the HR^35^ZE and historical HR^10^ZE groups that received at least one dose of treatment with an unfavorable outcome after 8 weeks of experimental treatment start. According to the clinical and laboratory information, participants will be classified as having an unfavorable outcome if they suffered one or more grade ≥ 3 AE or SAE that are possibly, probably, or definitely related to rifampicin OR they did not complete their treatment because of other reasons OR were lost-to follow-up. High doses of rifampicin will be considered non-inferior to standard doses if the upper boundary of the 95% CI of the proportion of participants with an unfavorable outcome is less than 8% that of the point estimate in the historical standard dose group.

Efficacy will be assessed as the proportion of participants with pulmonary TB in the HR^35^ZE and the historical HR^10^ZE groups that have sputum culture conversion in liquid media at week 8. The unfavorable efficacy outcome will be defined as having a positive sputum culture at week 8.

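### Section 2.10 counts a dosed participant who withdraws consent, or stops because the diagnosis changed, as a primary safety failure; Table 2 lets the same person be removed from a safety set, and control capture of such failures is not assured.

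*Protocol article*

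**What the plan says.** Four parts of the protocol article bear on this.

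- **Section 2.10 (Main Outcomes Analysis).** The primary safety outcome is analysed in everyone in both groups who had at least one dose. Besides rifampicin-related grade 3 or higher or serious adverse events, the unfavourable outcome includes patients for whom "OR they did not complete their treatment because of other reasons OR were lost-to follow-up".
- **Sections 2.2 and 2.8.** The primary safety endpoint is the proportion with a grade 3 or higher or serious adverse event by week 8. The decision in 2.8 rests on "the upper limit of the 95% confidence interval of the difference of proportions in grade ≥ 3 AE", set against 8 points. Neither section makes non-completion an event.
- **Table 2, row 3 (modified intention to treat), Primary Safety column.** This set is the intention-to-treat population after "exclusion of some subjects in a justified way (subjects having non-tuberculous mycobacteria, early withdrawal of consent, etc". The Efficacy column has essentially the same wording. Table 2 does not rank its five sets.
- **Section 2.5 (Recruitment).** For the controls, "the records of all patients from that period with pulmonary and extrapulmonary rifampicin susceptible tuberculosis will be reviewed". The items to be captured are severe or grade 3 adverse events and week 8 microbiological status.

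**The concern.** Consider two people who have taken 35 mg/kg. One withdraws consent in the second week. The other entered with probable tuberculosis, which section 2.4 allows, grows non-tuberculous mycobacteria and stops. Under 2.10 both are safety failures. Under 2.2 and 2.8 neither is, unless an adverse event occurred. Under row 3 of Table 2 both may be absent, along with any event they had.

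Each treatment can mislead. Counting a change of diagnosis as a safety failure charges rifampicin with something unrelated to it. Removing early withdrawers hides intolerance if they left because they felt unwell. A changed diagnosis may justify exclusion from culture conversion, but it does not undo exposure. Because row 3 ends in an open list and the trial is open-label, further treated people could be excluded once their outcome is known.

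The two cohorts are also not on the same footing. A chart control has no trial consent to withdraw. Control non-completion and loss are part of the 2.10 outcome, but section 2.5 does not list them as extracted. If they are under-recorded, 2.10 adds failures mainly to the experimental cohort, in a comparison that turns on a few events.

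**Working it through.** **Inputs from the protocol.** Section 2.9: "the number of participants per arm has been calculated to be 134 participants"; "Alpha risk is set in 0.1 and power in 0.8"; "expected standard treatment grade ≥ 3 AE are 5–10% (mean 8%) among experimental arms and standard treatment arms"; "We assume that 5% of patients will not be assessable". Section 2.8: 95% interval of the difference, margin 8 points.

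**The plan's own figure.** n = 2p(1−p)(z₁₋α + z₁₋β)²/Δ², divided by 0.95 for the non-assessable.
- p = 0.10, one-sided α = 0.1: 2×0.10×0.90×(1.282+0.842)²/0.08² = 126.8, so 127; 127/0.95 = 133.7, so 134. This reproduces the stated number.
- p = 0.08 (the stated mean), one-sided α = 0.1: 103.7, so 104; 104/0.95 = 109.5, so 110.

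The 134 therefore matches the top of the stated rate range rather than its mean. That is a separate matter; below, 134 per cohort is taken as given.

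**Two-person check.** Upper limit U = (p₁−p₀) + 1.96×√[p₁(1−p₁)/n₁ + p₀(1−p₀)/n₀], treating the cohorts as independent. Assume 11/134 = 8.2% with an adverse-event outcome in each cohort, plus two other participants who withdraw or are reclassified.

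| Handling | Experimental | Control | U (points) | Below 8? |
|---|---|---|---|---|
| Kept, not counted as events (2.2, 2.8) | 11/134 | 11/134 | 6.6 | yes |
| Counted as failures (2.10) | 13/134 | 11/134 | 1.49 + 1.96×3.49 = 8.3 | no |
| Removed (Table 2, row 3) | 11/132 | 11/134 | 0.12 + 1.96×3.38 = 6.7 | yes |

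Across the Wald, Newcombe and Miettinen–Nurminen methods, the counted case runs from 8.3 to 8.7 and the removed case from 6.7 to 7.1.

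**How far this generalises.**
- Control rate near 10% (13 events): 15/134 v 13/134 gives 8.8; 13/132 v 13/134 gives 7.3. Two people still suffice.
- Control rate near 5% (7 events): 9/134 v 7/134 gives 7.2 and passes; 10/134 v 7/134 gives 8.1, so three are needed.
- 90% interval (z = 1.645): 13/134 v 11/134 gives 7.2 and passes; 14/134 gives 8.1, so three are needed.
- Literal wording of 2.10, in which the upper bound of the experimental proportion alone is set against the control estimate plus 8 points (8.21 + 8 = 16.21%): 13/134 has an upper bound of 14.7% (Wald) or 15.9% (Wilson) and passes. Three more failures (Wilson, 16.8%) or four (Wald, 16.5%) are needed.
- One matching control failure: 13/134 v 12/134 gives 7.7 and passes. Two in each cohort: 13/134 v 13/134 gives 7.1 and passes.

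**Unequal ascertainment.** This is the chance that U falls below 8, by exact enumeration with 134 per cohort and an 8% event rate in both. The 5% failing for these other reasons is illustrative; it equals the plan's non-assessable share. With it, the unfavourable rate is 0.08 + 0.05×0.92 = 12.6%. With half as much it is 0.08 + 0.025×0.92 = 10.3%.

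| Experimental v control rate | Chance of passing |
|---|---|
| 8% v 8% | 0.68 |
| 12.6% v 8% (no control failures recorded) | 0.16 |
| 12.6% v 10.3% (half as many in controls) | 0.32 |
| 12.6% v 12.6% (equal) | 0.52 |

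**Removal, if the modified set decided.** With a true experimental rate of 16% v 8%, false non-inferiority is 0.029. If 5% withdraw early and half of them had events (an assumption), removing them leaves (0.16−0.025)/0.95 = 14.2% in 127 people, and false non-inferiority becomes 0.075.

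**The case against.** The strongest reply is that 2.10 already fixes the primary analysis: everyone with at least one dose, which is the intention-to-treat row of Table 2. Nothing makes the modified set decisive, and people removed from it stay in the primary set with their events. Differing results across sets are what sensitivity sets are for. The article is also a condensation, so a closed exclusion list or a ranking of sets may stand in the full protocol. This has weight. It means the discrepancy is between two analysis sets, and not a demonstrated corruption of the primary one.

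A reader might also infer that these failures cannot occur among controls. The documents do not support that. Section 2.5 aims to include all eligible patients treated in 2017–2019, without requiring completion, and 2.10 applies non-completion and loss to the historical group as well. Only withdrawal of trial consent is confined to the prospective cohort. Nor does section 2.5 say that controls are chosen on the final diagnosis; that reclassified cases would be rare among them is an inference. Row 3 also does not name early stopping as an exclusion. It names non-tuberculous mycobacteria and early consent withdrawal.

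What the objection leaves standing is the mismatch of 2.10 with 2.2 and 2.8, the removal of exposed people from a set labelled for primary safety, the open list, and the silence on capturing control non-completion. The first lies in the endpoint definition itself and is not a detail that the article simply leaves out.

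**Conclusion.** The point holds in limited form. The article gives three treatments of one dosed person: failure (2.10), not an event (2.2 and 2.8), and removable (Table 2, row 3). It does not ensure that the failures counted in 2.10 are ascertained alike in both cohorts.

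At a control rate of about 8–10%, with a 95% interval of the difference and no matching control failures, two such participants separate a pass from a fail (6.7 v 8.3 points at 11 control events). It would be too strong to say that two people reverse the trial's verdict in general: at a 5% rate or with a 90% interval three are needed, under the literal wording of 2.10 three or four, and one matching control failure undoes the reversal. Likewise, the fall in the chance of passing from 0.68 to 0.16 is an extreme in which no control failure of this kind is recorded; with equal capture the figure is 0.52. The 0.075 applies only if the modified set were decisive, which the article does not say.

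The correction is worth making before analysis, because the margin turns on very few people and the change is mostly wording.

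**What to change.** 1. Name the at-least-one-dose set as decisive for primary safety. Keep every dosed participant in it, with all adverse events recorded up to withdrawal or week 8.
2. Remove row 3 of Table 2 for primary safety, or close its list of exclusions and label the set supportive.
3. Reconcile 2.10 with 2.2 and 2.8 so that consent withdrawal or a change of diagnosis is not in itself a safety event.
4. Extract non-completion and loss to follow-up from the control records, and report both, with reasons, by cohort.
5. Keep diagnosis-based exclusion for efficacy, applied by the same rule in both cohorts.

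The cost is a wording change in Table 2 and section 2.10, slightly more chart extraction, and loss of the discretion to exclude treated people afterwards. No extra patients or visits are needed.

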## 1. Introduction

Current standard treatment for drug susceptible tuberculosis (DS-TB) was designed 40 years ago and has remained unchanged except for a 4-month regimen using high-dose rifapentine and moxifloxacin following the results of a recent clinical trial [1]. Rifampicin is still the backbone drug in the treatment of DS-TB because of its potent bactericidal and sterilizing activity. The currently used once daily 10 mg/kg dosing of rifampicin was selected in the 1970s and was based on pharmacokinetics, toxicity, and cost concerns [2]. Under clinical trial conditions and using per protocol analysis, the current standard regimen achieves a 95% efficacy [3]. However, several pharmacological, bacterial, and host factors may negatively affect treatment outcomes in daily practice.

Some groups of people are more vulnerable to TB because of risk factors (e.g., advanced age, immunosuppression, diabetes, or liver disease) that increase their risk of active disease and poor treatment outcomes [4]. For example, treatment success rate was 86% globally, but only 77% for people living with HIV [5]. Drug-induced liver injury is the best-known adverse reaction associated with rifampicin, isoniazid, and pyrazinamide. In addition, rifampicin typically causes gastrointestinal symptoms and hypersensitivity reactions (pruritus, rash, flu-like syndrome, hemolytic anemia). Although for clinicians these groups are also considered more vulnerable to adverse reactions, different studies show contradictory results. For example, in a retrospective study including 1149 patients, age > 60, diabetes, and hepatitis B virus (HBV) infection were not associated with an increased risk of adverse reactions [6].

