### 2.2. Objectives and Endpoints

The study primary objective is to evaluate the safety of high-dose rifampicin (35 mg/kg/d) as part of a standard first line regimen using standard doses of isoniazid (5 mg/kg), pyrazinamide (25 mg/kg), and ethambutol (15–25 mg/kg) for 8 weeks in adult subjects with pulmonary or extrapulmonary DS-TB belonging to difficult to treat subgroups. The secondary objectives are to evaluate the tolerability, efficacy, bactericidal activity, pharmacokinetic/pharmacodynamics, and cost effectiveness of high dose rifampicin, among others. 

The primary safety endpoint is the proportion of participants and historical controls with one or more grade 3 or higher adverse events (AE) according to the CTCAE v5 or SAE at 8-weeks after treatment with high-dose rifampicin onset. Table 2 below describes in detail the analysis population and primary safety outcomes. The secondary tolerability endpoint includes the proportion of participants with any AE. The secondary efficacy endpoint includes the proportion of participants and historical controls who have sputum culture conversion at 8 weeks after treatment onset or a proportion of participants with clinical improvement according to the treating physician (if follow-up images are available for extra-pulmonary TB) but without a follow up sample at 8 weeks after treatment onset.

Most TB phase 2 trials complete their intervention at week 8 or earlier and then participant care is transferred to a public institution within the National TB programs, so the information about end of treatment and post-treatment outcomes is scarce [10,17,18]. In the RIAlta trial, after the intervention and the primary safety objective evaluation, an extended follow-up period will be offered to participants, in line with the phase 2b/c design suggested by Phillips et al. [19]. This will provide information about end-of-treatment outcomes and relapse incidence in the prospective group.

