### 2.7. Rifampicin Dosing Strategies

Study participants will receive high dose rifampicin 35 mg/kg for 8 weeks (maximum once daily dose of 3150 mg) by combining fixed-dose combination (FDC) tablets with rifampicin loose capsules (Table 3). We have adapted the WHO guidelines weight band dosing scheme for a more accurate rifampicin dosing. The dose for each band was calculated for the medium weight in each band (45 mg × 35 mg = 1575 mg, rounding 1500 mg), and for those with >80 kg, the dose is calculated for 90 kg (90 mg × 35 mg = 3150 mg).

One limitation is the scarcity of the 600 mg presentation for rifampicin, which would reduce the pill burden for the participants in this trial. For instance, as optimized doses of rifampicin come closer to daily practice, public health decision makers should advocate to increase the availability of rifampicin in high dose presentations to reduce the number of pills taken by patients.

To achieve a similar drug exposure to oral rifampicin at 35 mg/kg/day, the dose for intravenous administration should be 26 mg/kg/day [13].

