Therefore, the population included in this study belong to the other risk factors groups for failure and relapse that have been under-represented in previous clinical trials [4,22]. As a phase 2 study, the main aim of this clinical trial is to evaluate safety of rifampicin defined as the rate of participants suffering grade 3 or higher adverse events or severely adverse events. This information will be likely available from historical controls although it was not systematically collected. Grade 1–2 adverse events, which are considered tolerability problems, are not typically reported in clinical records, or the information about them is not complete, thus making it difficult to make comparisons. To address this, we have developed adverse events monitoring and management guidelines, which will be harmonized at all centers for the prospective part. Extensive training will be provided to the investigators at each site. 

It is important to acknowledge the main limitations related to this trial design. Because of the limited recruitment capacity within our consortium and budgetary constraints, we decided to use historical controls (rifampicin 10 mg/kg along with the same TB regimen) and assign all prospectively recruited participants to the 35 mg/kg dose. This results in a non-randomized design as all participants will be assigned to the experimental arm and compared with historical controls. Hence, another limitation is that information about tolerability is often incomplete or not reported in clinical records, and the endpoints in the different sub-studies are not performed in daily clinical practice. For similar reasons, the sample size is too small for a formal subgroup analysis. The results will inform a larger phase 3 trial with power calculations for relevant subgroups.

Having one PK sampling at week 4 will allow us to show the percentage of participants reaching the target exposure (AUC/MIC) when in a steady state after rifampicin induction of its own metabolism. In contrast, this approach will not provide information about exposure during the first week of treatment, when most of the bacterial killing occurs. Nevertheless, this knowledge will aid our understanding if optimized rifampicin dosing is more likely to meet target rifampicin exposure. 

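### Table 3 gives three fixed-dose tablets up to 60 kg, so participants of 56–60 kg fall below the protocol's own ethambutol range and well under its isoniazid and pyrazinamide doses

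*Protocol article*

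**What the plan says.** Section 2.2 (Objectives and Endpoints) defines the background regimen as "standard doses of isoniazid (5 mg/kg), pyrazinamide (25 mg/kg), and ethambutol (15–25 mg/kg) for 8 weeks". Ethambutol has a range; isoniazid and pyrazinamide each have a single nominal dose.

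Section 2.7 (Rifampicin Dosing Strategies) says the high rifampicin dose is reached "by combining fixed-dose combination (FDC) tablets with rifampicin loose capsules (Table 3"). It adds that the WHO weight bands were adapted to make rifampicin dosing more accurate, with each band's dose set at its middle weight. Table 3 gives the content of one fixed-dose tablet as "150 mg rifampicin, 75 mg isoniazid, 400 mg pyrazinamide, and 275 mg ethambutol". The fixed-dose entry is "450 mg 3 tablets" in the 35–40, 41–50 and 51–60 kg bands, and "600 mg 4 tablets" at 61–70 kg. The article mentions no separate isoniazid, pyrazinamide or ethambutol.

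The Discussion describes the comparator as "historical controls (rifampicin 10 mg/kg along with the same TB regimen"). The Introduction states: "Drug-induced liver injury is the best-known adverse reaction associated with rifampicin, isoniazid, and pyrazinamide".

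**The concern.** The tablet count stays at three from 35 to 60 kg while the loose rifampicin rises. This keeps rifampicin near 35 mg/kg but lets the companion drugs thin out as weight increases. At the top of the 51–60 kg band the table no longer delivers the regimen that Section 2.2 describes.

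Two things are at stake. First, participants from vulnerable groups would spend eight weeks below the protocol's own companion doses. Second, the comparison with controls is supposed to differ only in rifampicin. If controls of the same weight received more isoniazid and pyrazinamide, both recognised in the Introduction as causes of liver injury, part of any safety similarity could come from the lighter background regimen. The same difference would work against the experimental arm on week-8 culture conversion.

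**Working it through.** **Inputs.** One fixed-dose tablet holds rifampicin 150 mg, isoniazid 75 mg, pyrazinamide 400 mg and ethambutol 275 mg (Table 3). Tablet counts and weight bands are from Table 3; stated doses are from Section 2.2.

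**Table 3's own rifampicin totals.** Total = loose rifampicin + 150 mg × fixed-dose tablets:

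- 35–40 kg: 900 + 450 = 1350 mg
- 41–50 kg: 900 + 150 + 450 = 1500 mg
- 51–60 kg: 1500 + 450 = 1950 mg
- 61–70 kg: 1500 + 150 + 600 = 2250 mg
- 71–80 kg: 1800 + 150 + 750 = 2700 mg
- ≥80 kg: 2400 + 750 = 3150 mg

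All six match the printed totals, so the three-tablet entry at 51–60 kg is not a reading error.

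**Companion doses at 51–60 kg.** Three tablets give isoniazid 3 × 75 = 225 mg, pyrazinamide 3 × 400 = 1200 mg and ethambutol 3 × 275 = 825 mg. The dose per kg is mg divided by weight:

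| Weight | Ethambutol (floor 15) | Isoniazid (stated 5) | Pyrazinamide (stated 25) |
|---|---|---|---|
| 51 kg | 16.2 | 4.41 (−12%) | 23.5 (−6%) |
| 55 kg | 15.0 | 4.09 (−18%) | 21.8 (−13%) |
| 56 kg | 14.7 | 4.02 (−20%) | 21.4 (−14%) |
| 60 kg | 13.75 | 3.75 (−25%) | 20.0 (−20%) |

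Ethambutol meets its floor at 825/15 = 55.0 kg exactly, so every weight from 56 to 60 kg is below range.

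**Comparison across bands (mg/kg).** Mid-band weights are 37.5, 45.5, 55.5, 65.5 and 75.5 kg, and 90 kg for the open top band (the weight Section 2.7 uses there).

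| Band | Tablets | Ethambutol across band | Mid-band ethambutol | Mid-band isoniazid | Mid-band pyrazinamide |
|---|---|---|---|---|---|
| 35–40 kg | 3 | 23.6–20.6 | 22.0 | 6.00 | 32.0 |
| 41–50 kg | 3 | 20.1–16.5 | 18.1 | 4.95 | 26.4 |
| 51–60 kg | 3 | 16.2–13.75 | 14.9 | 4.05 | 21.6 |
| 61–70 kg | 4 | 18.0–15.7 | 16.8 | 4.58 | 24.4 |
| 71–80 kg | 5 | 19.4–17.2 | 18.2 | 4.97 | 26.5 |
| ≥80 kg | 5 | 17.2 at 80 kg, falling | 15.3 | 4.17 | 22.2 |

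The 51–60 kg band is the only closed band that leaves the ethambutol range, and it has the lowest mid-band dose of all three drugs. In the open top band ethambutol also falls below 15 mg/kg, above 1375/15 = 91.7 kg.

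**Step at the band edge.** Between 60 and 61 kg the count goes from three to four and each companion dose rises by a third in mg. At 61 kg ethambutol is 1100/61 = 18.0, isoniazid 300/61 = 4.9 and pyrazinamide 1600/61 = 26.2 mg/kg.

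**Contrast with controls.** Isoniazid 5 mg/kg at 75 mg per tablet and rifampicin 10 mg/kg at 150 mg per tablet both imply weight/15 tablets: 56/15 = 3.7 and 60/15 = 4.0. If a control of this weight took four tablets (assumption), the experimental participant receives 3/4 of each companion drug, or 25% less.

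**Number affected.** The article gives no weight distribution. If 10–20% of the 134 participants weigh 56–60 kg (assumption), that is 13 to 27 people.

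**The case against.** The strongest reply accepts the arithmetic and disputes its weight.

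- **Only ethambutol breaches a stated limit, and narrowly.** The shortfall from 15 mg/kg is 1.8% at 56 kg and 8.3% at 60 kg. Isoniazid and pyrazinamide have single nominal doses that any banding scheme will miss; the same table runs 29% over on isoniazid and 37% over on pyrazinamide at 35 kg. This stands as a ranking of the evidence: ethambutol is the firm contradiction. The isoniazid and pyrazinamide figures are still correct, and 25% is the largest isoniazid shortfall in any closed band.
- **The full protocol may allow separate companion drugs.** Table 3 is titled as rifampicin dosing, and the article is a condensed account. That is possible, but the article describes only loose rifampicin as an addition, and the dose changes in Section 2.6 concern drug interactions. The conflict between Section 2.2 and Table 3 remains on the page.
- **Bias is inferred.** Control tablet counts are not given, and weight is not a matching variable. If local practice used three tablets at this weight, there is no contrast. Section 2.10 also counts adverse events only when they are at least possibly related to rifampicin, which dilutes any effect of isoniazid or pyrazinamide. Both points stand; they limit the bias argument to a direction.
- **The remedy moves pyrazinamide from 14% under to 14% over at 56 kg**, in a population that includes people with liver disease. This is true and deserves clinical agreement, but 28.6 mg/kg lies within the spread the table already accepts (up to 34.3 mg/kg at 35 kg).

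**Conclusion.** The concern holds. Table 3 does not deliver the companion regimen stated in Section 2.2 for participants of 56–60 kg. Ethambutol is 14.7 to 13.75 mg/kg against a floor of 15; isoniazid is 20–25% and pyrazinamide 14–20% below the stated dose. These figures need only the table and the stated doses, and they assume that no separate companion drugs are given, since none is described.

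The effect on the comparison is less certain. It depends on controls of this weight having taken four tablets. Only its direction can be given, towards the experimental arm on safety and against it on week-8 culture, because the article gives no dose-response for these drugs. The count of 13 to 27 participants rests on the assumed 10–20% share. The point should be corrected, but it does not undermine the design.

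**What to change.** Split the 51–60 kg band at 55 kg.

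- **51–55 kg:** keep three fixed-dose tablets and five 300 mg rifampicin units. Ethambutol stays at 16.2–15.0 mg/kg.
- **56–60 kg:** give four fixed-dose tablets, four 300 mg and one 150 mg rifampicin units. Rifampicin is 600 + 1200 + 150 = 1950 mg, unchanged. Ethambutol becomes 1100/56 = 19.6 to 1100/60 = 18.3 mg/kg, isoniazid 300/56 = 5.4 to 300/60 = 5.0, and pyrazinamide 1600/56 = 28.6 to 1600/60 = 26.7.

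In the same edit, state whether the companion doses are deliberately capped in the top band, where ethambutol falls below 15 mg/kg above 91.7 kg.

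The cost is one added column in Table 3 and on the site dosing card, and nine units a day instead of eight for participants of 56–60 kg. The rifampicin dose, sample size and analysis do not change. Section 5 places first recruitment in late 2022 or early 2023, after the article was written, so the change could be made before first dosing.
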